### Study setting

This pilot study is carried out at the Institute of Memory and Cognition, Tallaght University Hospital, Dublin, Ireland which is a tertiary referral centre at a University teaching hospital. The Institute is coordinated by Consultant Geriatricians and a Consultant Neurologist with consensus diagnosis for cognitive impairment undertaken with specialised Advanced Nurse Practitioner, Occupational Therapist, Speech and Language Therapist and Neuropsychologist input.

### Eligibility criteria

VINCI-AD will recruit both males and females with a diagnosis of amnestic MCI as determined by consensus diagnosis at the Institute of Memory and Cognition. Those eligible for inclusion in VINCI-AD will have an index delayed memory score on the Repeated Battery of Neuropsychological Status (RBANS) of less than 85 (indicative of amnestic features) and a score of 0.5 on the Clinical Dementia Rating Global scale indicating mild impairment not impacting daily function. All participants mut be on stable medications for one month prior to recruitment, must have sufficient understanding of English language and must be able to provide informed consent. VINCI-AD exclusion criteria include:

Significant current depressionUncorrected vision/hearing lossHistory of brain surgeryHistory of epilepsy with any seizure event in last yearPrescribed any pharmacological agents known to significantly increase seizure riskDiagnosed arrhythmia including atrial fibrillationCardiac pacemaker implantExisting left ear deformity or recent ear traumaAlcohol dependencePrescribed DMARDs or immunotherapies

### Assessment procedures

Participants will undergo a baseline visit to assess eligibility by the study clinician (HD). This baseline visit will include a detailed clinical review to encompass clinical, demographic and anthropomorphic data, cognitive history and medication review (please see Additional File 1 for baseline assessment proforma).

### Intervention

Participants will receive active and sham stimulation with the NEMOS © CerboMed tVNS device. Two small electrodes emit a low-voltage electric signal which permeates the skin. When the electrodes are placed at the cymba conchae of the ear, stimulation actives the afferent branch of the VN that innervates the skin of the ear (Arnold’s nerve). The electric signal consists of an 8 Hz frequency wave with participant-selected amplitudes ranging from 0.1 mA to 5 mA depending on their sensory threshold, the signal cycles of 200 ns and comes in 30 s on – 30 s off bursts. For the sham condition the electrode is placed on the earlobe which is free of vagus innervation. For the active condition it is placed on the cymba conchae of the left ear. At each stimulation study visit the device is explained to the participant and then fitted by the study researcher. Participants are given oral and written instructions at each stimulation study visit regarding how to set up and fit the device in their ear.

### Safety and tolerability of tVNS in MCI

The risk associated with use of the NEMOS © Cerbomed tVNS device is minimal as published data of the safety profile shows minimal adverse events. The most common adverse events reported include local skin tingling, burning, redness, itching, tinnitus or headache which occur in up to 18% of participants, and tends to resolve quickly after discontinuation of the use of the device [42]. Due to the theoretical risk of increasing cardiac vagal-mediated bradycardias or hypotensive episodes by stimulating the right VN, participants will have stimulation of the left ear only.

During the active and sham stimulation conditions, safety will be recorded by completion of the following:

Contemporaneous recording of any adverse events reported by participants whilst undergoing either active or sham stimulation.Likert-Based Questionnaires (See Additional File 2) will assess for established side effects previously reported with tVNS: pain, skin discomfort, tingling, headache and tinnitus. These will be administered both during active and sham stimulation.Detailed assessment of subjective (OH symptoms including faintness, light-headedness), peripheral (beat-to-beat blood pressure) and central (TSI) haemodynamic responses to active stand.
Briefly, participants will undergo active stand from supine to standing. After lying supine for 5 min, participants will be asked to stand as fast as they can. Beat-to-beat blood pressure and heart rate responses (assessed via the Finapres© NOVA) will be monitored during active stand and for three minutes after. To standardise assessments, all assessments are all taken at the same time each day, and all routine medications are taken as usual each morning. OH is defined by consensus as a sustained reduction of systolic blood pressure (SBP) of at least 20 mmHg or diastolic blood pressure (DBP) of 10 mmHg within 3 min of standing [43].
During active stand, cerebral oxygenation (TSI) will be estimated using NIRS-based analysis software. TSI analysis will be undertaken using the PortaLite OxySoft© NIRS device (PortaLite, Artinis Medical Systems B.V., Elst, The Netherlands) and the light emitting diode will be placed on clean skin on the right forehead, devoid of moisture or oil, and secured with a black headband. TSI readings are transferred via Bluetooth in real-time and will give an approximation of tissue oxygenation during rest, active stand, and all cognitive assessments.

Following assessment, participants will be given contact details of the principal investigator and study coordinator at the hospital who they can contact if they have concerns, or any new symptoms arise. Any adverse events will be diarised during the intervention and closely monitored until resolution. Data of participants who discontinue or deviate from the study protocol will be retained for intention to treat analysis.

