## Methods/design

### Study design

VINCI-AD is a single-site, single-blind, sham-controlled crossover pilot study in patients with amnestic MCI. Each participant is assessed at baseline (no stimulation) followed by randomisation to both sham stimulation and active tVNS stimulation over two subsequent study visits. The study comprises a baseline assessment (visit 1) followed 7–10 days later by either an active or sham stimulation study visit and again 7–10 days later by a third visit wherein the final condition (active or sham) will be undertaken. The inclusion of a sham stimulation condition is to confound for potential unblinding, which is common in device trials. Participants will be enrolled and consented by study clinician (HD). Please see Fig. 1 for an illustration of randomisation and sham stimulation technique.

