**Fig. 1 Fig1:**
[figure not shown]
Method of crossover

Our study will follow the Standard Protocol Items: recommendations for Interventional Trials (SPIRIT) guidelines [41]. Table 1 illustrates the SPIRIT flow diagram summarising study procedures, outcome measures, randomisation and assessments for each study visit.

**Table 1 Tab1:** Flowchart of VINCI-AD Protocol Timeline

			Study Period					
			Screening (day − 90 to day − 7)	Visit 1 (day 0)		Visit 2 (day 7–10)		Visit 3 (day 14–17)
Enrolment								
- Eligibility Screen			x					
- Informed Consent			x					
Intervention								
- Baseline assessments (no stimulation)				x				
- Active (left cymba conchae) stimulation						ø		ø
- Sham (left earlobe) stimulation						†		†
Assessments								
- General assessment, vitals, medication changes				x		x		x
- Primary Outcome: Safety								
- Assess for AE/ SAEs						x		x
- Active stand with TSI				x		x		x
- Primary Outcome: Acceptability and Tolerability								
- Likert scale questionnaires						x		x
- Cognitive assessments								
- FNAT				x		x		x
- SART				x		x		x
- SHQ				x		x		x
- Verbal word learning				x		x		x
- Semantic fluency				x		x		x
- Digit span forwards				x		x		x
- Digit span backwards				x		x		x
- Verbal word recall				x		x		x
- Verbal word recognition				x		x		x
- Frontal Oxygenation								
- Cognitive testing TSI				x		x		x
- Neurocardiovascular assessments								
- HRV				x		x		x
- Serum / Plasma venepuncture								
- Inflammatory cytokine panel				x		x		x
- Device usability assessment								
- Kettle test								x

Ø = active stimulation randomisation: participant randomised to either sham or active stimulation at Visit 2 and alternative stimulation site at Visit 3

† = sham stimulation randomisation: participant randomised to either sham or active stimulation at Visit 2 and alternative stimulation site at Visit 3

AE – Adverse event; SAE – Serious adverse event; FNAT – Face Name Association Task; SART – Sustained Attention Response Task; SHQ – Sea Hero Quest Tas; NIRS – functional Near Infrared Spectroscopy; HRV – Heart Rate Variability; TSI – Tissue Saturation Index

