### Statistical analysis

VINCI-AD will assess the safety and feasibility of tVNS in older adults with MCI. All participants will be included in final analysis in an “intention-to-treat” fashion. Statistical analysis will be conducted using MATLAB (The MathWorks, Inc., Natick, MA, USA), SPSS (IBM SPSS Statistics for Windows, Armonk, NY: IBM Corp) and GraphPad Prism (GraphPad Software, Inc., San Diego, CA, USA). We anticipate that TSI analysis will require cleaning to remove “noisy” channels i.e. removing large spikes (changes in oxy-Hb larger than 0.5 mM/mm in amplitude); noisy channels will be excluded from analyses and data analyses will utilise software Platform for Optical Topography Analysis Tools [56] with a bandpass filter with cut-off frequencies of 0.01–0.8 Hz to remove instrumental or physiological noise [57].

In the first instance, descriptive statistics will be described for the cohort, reported as means (with standard deviations) or medians (with inter-quartile ranges) and proportions (percentages) as appropriate.

The primary aim of the current study is to assess the safety and feasibility of tVNS in MCI. To assess safety, a chi-square test will compare the number of adverse events reported during the active vs. sham condition. Further safety assessment will elicit symptoms experienced during active stand (using a chi-square statistic), peripheral (beat-to-beat blood pressure response to orthostasis – using mixed-effects linear regression with study condition as the independent variable, with random intercepts for study participant) and central (TSI – also assessed using a linear mixed-effects model). Feasibility will be reported via recruitment rates, successful enrolment, and study completion in proportions and percentages. Tolerability will be assessed using Likert scales, which will be compared between active and sham conditions using paired between-condition statistics (t-test if normally distributed or non-parametric equivalent). Descriptive statistics will be used to report acceptability using the modified Kettle test.

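### Side-effect symptoms have no stated unstimulated score, so per-condition symptom levels, and effects common to active and sham, cannot be separated from symptoms participants already have

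*Protocol article*

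**What the plan says.** The section on safety and tolerability opens its list of safety measures with "During the active and sham stimulation conditions, safety will be recorded by completion of the following". One item on that list is a set of Likert questionnaires (Additional File 2) that "will assess for established side effects previously reported with tVNS: pain, skin discomfort, tingling, headache and tinnitus". On timing, the article says: "These will be administered both during active and sham stimulation".

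Table 1 agrees. The row "Likert scale questionnaires" is marked at Visits 2 and 3 only, as is the row "Assess for AE/ SAEs". Visit 1 is the unstimulated visit: "Each participant is assessed at baseline (no stimulation) followed by randomisation to both sham stimulation and active tVNS stimulation". Active stand, cognition, HRV and cytokines are all marked at Visit 1 as well as at Visits 2 and 3.

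The Statistical analysis section says: "Tolerability will be assessed using Likert scales, which will be compared between active and sham conditions using paired between-condition statistics", by t-test or a non-parametric equivalent. It mentions no pre-stimulation score, no change score and no rule for symptoms that are new or have worsened.

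**The concern.** Pain, headache, tinnitus and skin discomfort can all occur without a device, and the Eligibility criteria do not exclude people who have them. Three participants can then give the same during-stimulation score: one with long-standing tinnitus that stimulation leaves unchanged, one who arrived with a headache, and one whose headache began after switch-on. Only the third describes a possible effect of stimulation.

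Safety and tolerability are primary outcomes in Table 1. A pilot's readers will want to know how people with MCI felt under active tVNS, and may set that level against the article's own figure of up to 18% for common side effects. They will also want to know about effects that stimulation produces at either site. The article describes sham as the same device placed on the earlobe, so discomfort common to both sites drops out of active minus sham. Only an unstimulated score could show it. The schedule fixes this timing, and no later analysis plan can subtract a score that was not collected.

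**Working it through.** There is no figure in the plan to reproduce here. The sample size of 40 rests on earlier literature, with no effect size, SD or power stated, and the point concerns when a score is taken. The sums below show only the direction and possible size of the effect.

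**Inputs.** From the article: 40 participants, each receiving both conditions; common side effects in up to 18%. Assumed: 18% is the stimulation-caused rate *a* under active; a share *b* of 5% to 30% already has a symptom at both visits, independently of any caused symptom; where needed, the sham rate *s* is 9%.

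**1. Level under active stimulation.** Observed rate = 1 − (1 − b)(1 − a).

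| b | Observed rate, a = 18% | Of 40 |
|---|---|---|
| 0% | 18.0% | 7.2 |
| 5% | 1 − 0.95 × 0.82 = 22.1% | 8.8 |
| 10% | 1 − 0.90 × 0.82 = 26.2% | 10.5 |
| 20% | 1 − 0.80 × 0.82 = 34.4% | 13.8 |
| 30% | 1 − 0.70 × 0.82 = 42.6% | 17.0 |

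**2. Active minus sham, symptom yes or no.** Difference = (1 − b)(a − s). If a = s = 18%, it is 0 at every b, so background symptoms create no false excess. If a = 18% and s = 9%, the 9.0-point difference becomes 8.55, 8.1, 7.2 and 6.3 points at b = 5%, 10%, 20% and 30%. This is dilution towards zero.

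**3. Active minus sham, Likert score.** If a stable symptom adds the same amount to both scores, it cancels exactly in the paired difference. A simulation of 40 pairs (assumed true difference 0.3) raised the stable-symptom SD from 0 to 1 to 2. The mean active score rose from 0.50 to 1.30 to 2.09, while the mean paired difference stayed at about 0.30 and its standard error at about 0.16.

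**4. Symptoms present at one visit only.** Visits 2 and 3 are 7 to 10 days apart, so some symptoms will differ between them and will not cancel. Randomised order makes them noise and not bias. A paired t-test was simulated on additive scores (40 pairs, caused symptoms in 30% active and 5% sham, severity 1 to 3, all assumed). Power was 0.81 to 0.83 with stable symptoms in 0% to 30%. It fell to about 0.67 with 10% stable plus 5% visit-specific symptoms, and to just under 0.6 with 20% plus 10%.

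**The case against.** The strongest reply is that the planned comparison is paired and its order randomised, so it does not need a baseline to be fair. That stands. A reader might infer from the schedule that existing symptoms will be counted as tVNS side effects, or that active stimulation will look falsely worse than sham. The documents do not support either reading: stable symptoms fall in both members of the pair, and visit-specific ones fall on active or sham at random.

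A reader might also take the 22% to 43% range, or a large loss of power, as a forecast. Neither is one. The article plans no yes/no cut-off on the Likert items and gives no background rate. Its 18% is an upper figure for a symptom list that only partly overlaps these five items, and it is not presented as a caused rate. An exact paired yes/no test under the assumptions of step 4 shows a steeper fall, from about 79% power to about 60% and 41%, but that is not the planned test. The article sets no power target for tolerability either.

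Finally, Additional Files 1 and 2 and Fig. 2 are not shown, and the questionnaire might ask about new or device-related symptoms. That could soften the point. However, the stated timing and Table 1 provide no same-scale score without stimulation. The baseline clinical review and the general assessment at each visit are not described as scoring these symptoms.

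What the reply leaves untouched is the per-condition level and any effect shared by both stimulation sites.

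**Conclusion.** The point holds in a limited form, as a cheap improvement to a primary safety and tolerability outcome. As scheduled, the trial can compare symptoms between active and sham with little bias. It cannot say how much of the symptom level under active tVNS, or of the level common to both conditions, was there before the device was switched on. The size cannot be fixed from the article, because it depends on how many participants have these symptoms anyway. The paired contrast is largely protected from stable symptoms, with some dilution if items are bounded or reduced to yes or no, and is made noisier by symptoms that differ between visits. The conclusion rests on the article's stated timing being complete, which the supplementary files could qualify.

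**What to change.** In the safety and tolerability section and in Table 1, add the existing Likert items that can occur without the device (pain, headache, tinnitus, skin discomfort) at two points: once at Visit 1, and immediately before switch-on at Visits 2 and 3.

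In the Statistical analysis section, state that symptoms new or worsened from that day's pre-stimulation score will be reported for each condition, and that the change score will be compared between active and sham alongside the paired comparison already planned. The Visit 1 score then serves as the no-stimulation reference, as it already does for the active stand.

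The cost is a few minutes per visit on a questionnaire that already exists, and a sentence of analysis text. Asking beforehand may prime participants to notice symptoms, but equally under active and sham. For a participant who has already been stimulated, that day's pre-stimulation score cannot be recovered, so the change is worth making before further visits take place.

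### Safety falls under an unqualified intention-to-treat rule and is compared only on events reported during a condition; exposure, late events and their attribution need a stated rule

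*Protocol article*

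**What the plan says.** All references are to the protocol article.

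- **Population.** Statistical analysis states: "All participants will be included in final analysis in an “intention-to-treat” fashion". The section Safety and tolerability of tVNS in MCI, straight after its sentence on following adverse events, adds: "Data of participants who discontinue or deviate from the study protocol will be retained for intention to treat analysis". Neither makes an exception for safety.
- **Comparison.** Statistical analysis states that "a chi-square test will compare the number of adverse events reported during the active vs. sham condition". It names no denominator.
- **Recording window.** The safety section lists "Contemporaneous recording of any adverse events reported by participants whilst undergoing either active or sham stimulation" and later says: "Any adverse events will be diarised during the intervention and closely monitored until resolution".
- **Schedule.** In Table 1 the row "Assess for AE/ SAEs" is marked at Visits 2 and 3 only. Participants also receive contact details for the team, "who they can contact if they have concerns, or any new symptoms arise".
- **Order of events.** Under Randomisation, allocation follows the baseline visit and precedes any stimulation. Under Study design, the two stimulation visits are 7–10 days apart.

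**The concern.** Safety is part of the primary aim, and adverse events are its leading measure. Intention-to-treat protects a comparison of efficacy, but it suits harms poorly: a person who was not stimulated cannot have a stimulation-related event, so counting that person can only lower the rate. Analysing by randomised condition also blurs active against sham if a session is given at the wrong site.

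The event window raises a second problem, specific to the crossover. An event that starts after the Visit 2 session lies outside a comparison of events reported during a condition. If it is elicited at Visit 3, the other condition is then being given, and no rule says which condition it belongs to. An event that starts after the Visit 3 session meets no scheduled assessment and depends on the participant getting in touch. The cohort is selected for impaired delayed memory, so self-initiated reporting is a weak safeguard.

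What is at stake is the adverse event rate under active stimulation and the active–sham difference, which are main products of this pilot.

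**Working it through.** **Inputs.** Planned number 40 (Sample size). Reference rate for the common adverse events: up to 18% (safety section). The document gives no expected loss between visits and no share of events starting after a session, so both are assumed below. There is no figure of the plan's own to reproduce here: 40 rests on earlier studies, with no event rate, precision or dropout stated.

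**Step 1: can a randomised participant be unexposed?** Yes. Allocation precedes stimulation and the conditions fall on separate visits, so a participant may miss one or both. The Discussion itself expects repeated attendance to be challenging.

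**Step 2: effect on the rate.** Reported rate = rate among exposed × (number exposed ÷ 40).

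| Unexposed to a condition (assumed) | Calculation | Reported rate |
|---|---|---|
| 0 of 40 | 0.18 × 40/40 | 18.0% |
| 2 of 40 (5%) | 0.18 × 38/40 | 17.1% |
| 4 of 40 (10%) | 0.18 × 36/40 | 16.2% |
| 8 of 40 (20%) | 0.18 × 32/40 | 14.4% |
| 10 of 40 (25%) | 0.18 × 30/40 | 13.5% |

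**Step 3: effect on what zero events would show.** The exact two-sided 95% upper bound after zero events is 1 − 0.025^(1/n).

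- n = 40: 8.8%
- n = 36: 9.7%
- n = 30: 11.6%

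With a one-sided 95% bound, 1 − 0.05^(1/n), the figures for 40 and 36 are 7.2% and 8.0%. The direction is the same.

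**Step 4: effect of leaving out late events.** Reported rate = 18% × (1 − share starting after the session). Assumed shares of 10%, 25% and 50% give 16.2%, 13.5% and 9.0%. The upper end is unlikely for the common local effects, which the safety section says tend to resolve quickly.

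**Step 5: attribution.** Suppose events between visits are recorded at Visit 3 and counted there. For a participant who had active first, an active event moves to sham; for one who had sham first, a sham event moves to active. Overall this mixes the two conditions and tends to pull the difference towards zero. Within a single participant it can make active look better or worse.

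**The case against.** The strongest reply is that the denominator problem is inferred. The stated test compares a number of events and gives no denominator. Someone never stimulated has no active condition during which to report anything. Retaining the data of people who discontinue may mean only that events in those who then stop are kept, which protects safety reporting. Definitions of analysis sets are commonly left to an analysis plan, which is not shown. This stands in part. The absence of a named safety set is not the point; the point is that the article states an unqualified intention-to-treat rule and repeats it in the safety section.

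A reader might also infer that later events are never collected. The document does not support that. Participants can report new symptoms, recorded events are followed until they resolve, and the Visit 3 assessment could pick up events from the preceding 7–10 days. What remains is that the stated comparison is limited to events during a condition, with no attribution rule and nothing active after Visit 3.

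A reader might further infer that the unequal follow-up of Visits 2 and 3 favours one condition. Order is randomised, so if the two orders are about equally frequent the imbalance falls on both conditions and should roughly cancel in the active–sham comparison. If only in-session events are counted, the windows do not differ at all.

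Finally, wrong-site delivery may be rare, since an unblinded researcher fits the device, and the plan does not announce a zero-event bound. Both points are fair and limit the size of the problem.

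**Conclusion.** The point holds in a limited form. The population and event window that the article states suit harms poorly, and it gives no rule for events between visits. Unexposed participants counted as event-free, or late events left out, can only lower a condition's rate. Misattributed events mainly blur the contrast between conditions. It would go too far to say that the plan certainly puts unexposed people in the denominator, or that every part of it biases towards safety.

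The size cannot be known from the document. With 10% missing a session, 18% becomes 16.2%, and the zero-event bound would be given as 8.8% when the exposed number supports 9.7%. These figures rest on the assumed 10%, on the 18% reference rate (itself an upper figure) and on all 40 being used as denominator. The effect is nil if everyone is exposed as randomised and no event starts after a session. It is worth correcting because safety is a primary aim and the remedy costs little.

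**What to change.** 1. State that adverse events are analysed over sessions in which stimulation was started, by the site actually stimulated, with the number exposed to each condition as denominator. Keep intention-to-treat for the exploratory outcomes.
2. State the adverse event window. Use the assessment already scheduled at Visit 3, before stimulation begins, to ask about events since Visit 2, and count those under the Visit 2 condition.
3. Add one brief contact after Visit 3, over a matching interval of 7–10 days, so that both sessions are observed for the same time.

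**Cost:** a few sentences of analysis wording, one question on arrival at Visit 3 and up to 40 short calls. Reported adverse event rates may turn out slightly less favourable.
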